### Outcome measures

2.6

Baseline, post-intervention outcome variables, and potential confounders will be measured in both intervention and control groups. Measurements will be taken prior to starting the treatment and at the end, at the 12th week.

### Primary outcome measure

2.7

Pain intensity, as measured by the Numeric Pain Rating Scale (NPRS)^[46,47]^ will be the primary outcome, where 0 indicates “no pain,” and 10 indicates “worst possible pain.” At each measurement point of the study, patients of both groups will be asked to rate the average intensity of their pain over the past 7 days. This procedure has demonstrated a high degree of reliability.^[48]^

### Secondary outcome measures

2.8

Secondary outcome measures for this study will be: the impact of FM, pain catastrophizing, fear of movement, and sleep quality.

The impact of FM is measured by the Fibromyalgia Impact Questionnaire (FIQ).^[49]^ This is a 10-item questionnaire assessing the impact of different aspects of FM on physical functioning, work status, depression, anxiety, sleep, pain, stiffness, fatigue, and well-being. The total FIQ score is calculated using a pre-determined algorithm and ranges from 0 to 100, where a higher score indicates a greater impact. The FIQ is widely used as an outcome measure for patients with FM, and its reliability and validity have been demonstrated.^[49]^

Pain catastrophizing, as measured by the Spanish version of the Pain Catastrophizing Scale (PCS),^[50,51]^ is a self-administered questionnaire that evaluates inappropriate coping strategies and catastrophic thinking about pain. The PCS uses a Likert scale of 13 items comprising of three dimensions: rumination, magnification, and hopelessness. The range of the scale is between 13 and 52 points, where low scores indicate low catastrophization and high scores indicate high catastrophization. This scale has demonstrated consistent validity and reliability.^[50]^

Fear of movement, as measured by the Tampa Scale of Kinesiophobia (TSK),^[52]^ involves a questionnaire with 17 items. Each item is scored on a 4-point Likert-type scale that ranges from strongly agree (1) to strongly disagree (4). Total scores for the questionnaire range from 17 to 68 points, where higher scores indicate more fear of movement and/or (re)injury. This scale has demonstrated consistent validity and reliability.^[53]^

The quality of sleep will be evaluated with the Pittsburgh Sleep Quality Index (PSQI), which corresponds to a questionnaire of 24 items aimed at assessing aspects related to the quality, subjective estimation, latency, frequency, and severity of problems of sleep. The maximum score is 21 points, and its reliability and validity have been previously demonstrated.^[54,55]^

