### Sample size calculation

2.10

Sample size for this trial is based on an expected mean difference between groups of 2 points of the NPRS, which is the minimum clinically important difference.^[63]^ The mean assumed for the calculation was 5.95, with a standard deviation (SD) of 2.06 points, based on results of other randomized clinical trials.^[64]^ To detect this difference between the control and intervention groups, with a value of α = 0.05 (probability of committing a type I error) and a statistical power of 90%, a minimum of 22 patients per group is needed. This minimal sample size estimate has been increased by 20%, taking into consideration the potential dropouts, giving a total of 28 patients for each group. Sample Size was performed using the Stata SE software, version 15 (StataCorp, College Station, TX).

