### Statistical analysis

2.14

The continuous variables will be presented as mean and standard deviation, and the categorical variables as number and percentage. To determine whether parametrical statistical tests are appropriate for the analysis of the data, the fitting to normal distribution will be evaluated using both statistical (Shapiro–Wilk test) and graphical (normal probability plot) methods. To examine baseline differences, a Student t-test will be used with interval variables, and Chi-squared with nominal ones. Analysis of covariance (ANCOVA) will be used for differences between groups at twelve weeks in primary and secondary outcomes using continuous scales, with adjustment for baseline levels of outcomes, using group differences in the mean change from baseline to twelve weeks as dependent variable. Finally, in the event of possible losses or dropouts, a statistical analysis will be carried out by protocol and intention to treat.

Data will be processed independently by two researchers, and inconsistencies will be detected using the VALIDATE command of the Epi Info (CDC) software. After checking for true outliers and extreme values, data will be winsorized using results below the 1st percentile and above the 99th percentile of the distribution of variables. Prior to analyzing the data, we will check for missing data and consider applying imputation methods using chained equations.

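### The printed TSK item anchors conflict with the stated direction of the total if most items are statements of fear; section 2.8 should reconcile them before scoring

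*Protocol article*

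**What the plan says.** Section 2.8 (Secondary outcome measures) of the protocol article introduces the scale thus: "Fear of movement, as measured by the Tampa Scale of Kinesiophobia (TSK"), and adds that it "involves a questionnaire with 17 items". Two statements on scoring follow, one directly after the other.

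- Item level: "Each item is scored on a 4-point Likert-type scale that ranges from strongly agree (1) to strongly disagree (4").
- Total: "Total scores for the questionnaire range from 17 to 68 points, where higher scores indicate more fear of movement and/or (re)injury".

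The section mentions no reverse-keyed items and no recoding, and it prints no item. It cites sources for the instrument and for its validity and reliability.

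Section 2.14 (Statistical analysis) sets the analysis: "Analysis of covariance (ANCOVA) will be used for differences between groups at twelve weeks in primary and secondary outcomes using continuous scales", adjusted for baseline and with change to week 12 as the dependent variable. The TSK total goes into that model.

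**The concern.** On an agree/disagree scale of fear, agreeing with a fear statement shows more fear. With the printed anchors, agreement earns the fewest points, so the most fearful patient gets the lowest total. The next sentence reads the total the other way round.

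If the forms or the scoring sheet follow the item sentence and the report follows the total sentence, a fall in fear would be reported as a rise, and the reverse. Kinesiophobia is a named secondary outcome and part of the rationale: the introduction links it to poorer treatment outcomes, and section 2.5 gives reduced fear avoidance as an aim of the education component.

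The safeguards described would not be expected to catch this. The double processing in section 2.14 looks for inconsistencies, and two people applying the same printed rule will agree. Winsorizing at the 1st and 99th percentiles does not address direction. The statistician is blinded to group (section 2.12), so an odd direction in one arm would not stand out before unblinding.

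**Working it through.** **Inputs.** From section 2.8: 17 items, each scored 1 to 4; strongly agree = 1 and strongly disagree = 4; total 17 to 68, with high meaning more fear. Not in the document: the wording of the items. Let k be the number of items for which agreement means *less* fear, and vary k from 0 to 17.

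**Step 1: the stated range.** 17 × 1 = 17 and 17 × 4 = 68. The stated range reproduces. It is the same whichever end of the scale is coded 1, so it does not show which coding is meant, and a range check cannot detect the error.

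**Step 2: direction under the printed anchors, with no item inverted.**

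- Most fearful respondent: (17 − k) × 1 + k × 4 = 17 + 3k.
- Least fearful respondent: (17 − k) × 4 + k × 1 = 68 − 3k.

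| k | Most fearful | Least fearful | Agrees with the stated direction? |
|---|---|---|---|
| 0 | 17 | 68 | No |
| 2 | 23 | 62 | No |
| 4 | 29 | 56 | No |
| 6 | 35 | 50 | No |
| 8 | 41 | 44 | No |
| 9 | 44 | 41 | Yes |
| 17 | 68 | 17 | Yes |

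The two sentences agree only if 17 + 3k > 68 − 3k, that is k > 51/6 = 8.5, so k ≥ 9. They conflict for every k from 0 to 8, which means whenever at least 9 of the 17 items are statements of fear.

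**Step 3: size of the effect when all items are keyed the same way.** Reversing an item x gives 5 − x. Summed over 17 items, a total T becomes 17 × 5 − T = 85 − T. As an illustration only (these totals are not from the document), a true fall from 45 to 37 would be recorded as a rise from 85 − 45 = 40 to 85 − 37 = 48.

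In the ANCOVA, change is multiplied by −1 and baseline B becomes 85 − B. The constant 85 is absorbed by the intercept. The group coefficient keeps its size and p-value and changes sign. The same mirror result holds if reverse-keyed items are also inverted.

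**Step 4: size when reverse-keyed items are left unrecoded.** The distance between the two extreme respondents is (68 − 3k) − (17 + 3k) = 51 − 6k. It is 51 at k = 0 and 51 − 24 = 27 at k = 4. The score then runs backwards and is also compressed, so the group difference need not keep its size.

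**Step 5: after the anchors are swapped.** With strongly disagree = 1 and strongly agree = 4, and all items stating fear, the most fearful respondent scores 68 and the least fearful 17. This agrees with the stated direction. Any reverse-keyed items would still need inverting; otherwise the compression in step 4 remains.

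**The case against.** The best defence is that the article fixes the direction of the total, which is what governs interpretation. The anchor sentence is a one-line description of a published, cited instrument. A journal article condenses the full protocol, and item-level scoring keys usually sit in the instrument or the case report form. The likeliest explanation is a slip in describing the scale, with the forms themselves correct. The conflict also depends on item wording that the article does not give.

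Much of this stands. A reader might infer that the two sentences cannot both hold under any circumstances, or that the trial's kinesiophobia result will come out reversed. The document supports neither. The first needs the assumption on item wording. The second needs three things together: items that mostly state fear, printed anchors that were actually used, and no recoding before the total is interpreted. Nothing in the article shows that the forms or the Excel file use those anchors.

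What does not stand is that the point is merely left to a fuller document. The article does not omit the scoring rule; it states one, and on the natural reading of a fear scale that rule runs against the interpretation given next to it. No other section resolves this.

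**Conclusion.** The point holds in conditional form. Assuming at least 9 of the 17 items are statements of fear, the item anchors and the stated direction of the total in section 2.8 conflict. If the items are scored and the total is read exactly as printed, the sign of the kinesiophobia group difference is reversed. The reversal is an exact mirror, 85 − T, if all items are keyed the same way or reverse-keyed items are also inverted. Otherwise the score is compressed as well.

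Severity is moderate to low, and it would be overstated as a threat to the trial's main conclusion. One secondary outcome is involved. The primary outcome is the NPRS, and the sample size rests on an "expected mean difference between groups of 2 points of the NPRS", so neither is touched. The error can be undone without new data if the item responses are kept. It still merits correction before analysis, because neither the score range nor the double processing would show it.

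**What to change.** In section 2.8 (or a correction to it):

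- Reconcile the anchors with the stated direction, using the validated version that the article cites. Agreement with a fear statement must score higher.
- State which items, if any, are reverse-keyed and how they are recoded.

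Before analysis:

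- Check the forms in use, since recruitment began in April 2019, and the scoring formula in the Excel file.
- Recode as 5 minus the item score only where the reversed anchors were actually used. Then apply the cited version's rule for any reverse-keyed items. An item worded so that agreement means less fear already runs in the right direction under the printed anchors, so the two steps cancel and it stays as recorded.

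The cost is a sentence or two of corrected text and one check of the form and scoring sheet. No new data are needed.

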### Potential confounders

2.9

#### Clinical variables

2.9.1

The physical activity level will be assessed by the Global Physical Activity Questionnaire (GPAQ).^[56]^ This questionnaire was originally designed by the World Health Organization to be interviewer-administered in assessing physical activity. The questionnaire comprises of 16 items that quantify the participant's physical activity level within a normal active week in order to estimate the total weekly volume of moderate-to-vigorous physical activity. It includes three domains: work, transportation, and recreational activities. This questionnaire has demonstrated consistent validity and reliability.^[57]^

Age, sex, duration of symptoms (months), and central sensitization in the last three months will be evaluated.

Anthropometry and body composition: weight will be measured with the patient barefoot and in light clothing. Height will be measured using a wall stadiometer, with the patient barefoot and upright, and with the sagittal midline touching the back board. Body mass index (BMI) will be calculated as weight, in kg, divided by the square of the height, in meters (kg/m^2^).

#### Socioeconomic status

2.9.2

Education level will be classified as primary education (functionally illiterate, without any studies, or those not completed primary education), middle education (primary education, high school/secondary education, or baccalaureate) and university education (college or PhD degree).

The cognitive status of all patients will be evaluated using the MMST.^[58]^ This is the most commonly used test for standardized cognitive assessment in the clinical setting.^[59]^ Although the scores of patients with mild-to-moderate cognitive impairment could be influenced by a number of sociodemographic variables (such as age and educational level),^[60–62]^ we established the cut-off at 26/27 to ensure that patients could follow simple commands and therapeutic indications during treatment.

### Sample size calculation

2.10

Sample size for this trial is based on an expected mean difference between groups of 2 points of the NPRS, which is the minimum clinically important difference.^[63]^ The mean assumed for the calculation was 5.95, with a standard deviation (SD) of 2.06 points, based on results of other randomized clinical trials.^[64]^ To detect this difference between the control and intervention groups, with a value of α = 0.05 (probability of committing a type I error) and a statistical power of 90%, a minimum of 22 patients per group is needed. This minimal sample size estimate has been increased by 20%, taking into consideration the potential dropouts, giving a total of 28 patients for each group. Sample Size was performed using the Stata SE software, version 15 (StataCorp, College Station, TX).

### Recruitment

2.11

Recruitment of the participants begun in April 2019 and is expected to finish in December 2019. Information on the study goals and procedures will be verbally provided. The participants will also be invited to raise questions or doubts on any aspect of the study. Data confidentiality guarantees will be provided to participants by the principal investigator. Written consent will be obtained from all participants before registration, and participants may withdraw from the trial at any point in time without penalties. The written consent form includes information regarding the background and purpose of the study, therapeutic interventions, outcomes, and the expected benefits and drawbacks.

### Randomization and blinding

2.12

Participants will be allocated to each group in a random manner through a sequence of numbers generated by computer program before the selection process begins. The group assigned to each patient will be kept in a sealed envelope, with the objective of concealing the assignment from the researcher (Fig. 2). Given the nature of the therapeutic interventions studied, physiotherapists and patient blinding will not be possible. However, the evaluator and the statistician will not know to which group each evaluated subject belongs.

**Figure 2 F2:**
[figure not shown]
Flow diagram of patients through phases of clinical study.

### Data management

2.13

Information obtained on the measurements of each participant will be recorded on a paper print-out. The information will then be hand-written on a paper document case report form and entered into an Excel file for future statistical analysis. In compliance with the Personal Information Protection Act, the names of all participants will not be disclosed, and a unique identifier number, given during the trial, will be used to identify participants. All participants will be informed that the clinical data obtained in the trial will be stored in a computer and will be handled with confidentiality. The participants’ written consent will be stored by the principal investigator.

### Statistical analysis

2.14

The continuous variables will be presented as mean and standard deviation, and the categorical variables as number and percentage. To determine whether parametrical statistical tests are appropriate for the analysis of the data, the fitting to normal distribution will be evaluated using both statistical (Shapiro–Wilk test) and graphical (normal probability plot) methods. To examine baseline differences, a Student t-test will be used with interval variables, and Chi-squared with nominal ones. Analysis of covariance (ANCOVA) will be used for differences between groups at twelve weeks in primary and secondary outcomes using continuous scales, with adjustment for baseline levels of outcomes, using group differences in the mean change from baseline to twelve weeks as dependent variable. Finally, in the event of possible losses or dropouts, a statistical analysis will be carried out by protocol and intention to treat.

Data will be processed independently by two researchers, and inconsistencies will be detected using the VALIDATE command of the Epi Info (CDC) software. After checking for true outliers and extreme values, data will be winsorized using results below the 1st percentile and above the 99th percentile of the distribution of variables. Prior to analyzing the data, we will check for missing data and consider applying imputation methods using chained equations.

### Harms

2.15

Patients from both groups will have a logbook available during each session, in order to collect, assess, report, and manage the potential adverse effects of the interventions that will be performed in the study. According to the informed consent, patients who show an increase in symptoms after 48 h of the session will be immediately evaluated by an rheumatologist.

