### Interventions

2.5

This study will be a single-blinded, randomized controlled trial with two parallel groups. The intervention group will receive a multicomponent treatment based on physical exercise, cognitive behavioral therapy adding to a GMI program, and a TNE program. In the initial stage, TNE will be used to decrease pain, fear avoidance, and disability.^[32,36]^ The TNE component aims to educate individuals on how pain is processed by the nervous system,^[37]^ using images, examples, metaphors, and drawings, as needed, during twice-weekly sessions for 2 weeks, each session being an average of 60 min duration. To ensure a standardized TNE program, a systematic checklist will be developed. Patients will also receive a booklet summarizing the educational content of the session, including images, examples, and metaphors about chronic pain and about their clinical condition. Patients will be asked to read the TNE booklet at least once a day.

The GMI program will include three steps: laterality training, imagined movements, and mirror therapy. Laterality training is the first step in the GMI program, designed to improve the accuracy of the patient's cortical representation of his/her body. The patient trains by looking at left and right images of body parts in different positions using the Recognize application, created by the Neuro Orthopaedic Institute (NOI). The application records both accuracy and response time and allows the user to set the difficulty of the images by modifying context and background. Training is carried out for 1 h per day, in short sessions using 20 images. Laterality training will be progressed by increasing the number and difficulty of the images involved.

The second step of the GMI program will be imagined movements, aimed at preparing the patient to move. The exact instructions that will be given are: "imagine that you are involved with the body in the illustrated positions without really moving in. Imagine each position twice, and repeat the whole process three times a day.” Imagined movements will be involved with anterior flexion, abduction and rotations, depending on the body segment being treated. The patients will be provided with photographs or diagrams of the positions which are to be imagined. Imagined body movements are reported to activate the cortex in a similar way to executed movements.^[38]^

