The last stage of the GMI program will be mirror therapy. The patients will be instructed to look at the mirror image of the unaffected body segment and to move that body segment in different ways. This creates the illusion that the body is moving pain–free and provides strong, positive, sensory cortical feedback that movement does not have to be painful, and may disprove cognitions of the mind, thus allowing the patient to believe pain-free movement is possible.^[39]^ Individuals are instructed to assign a body segment with the greatest symptomatology in the last 7 days.^[40]^ Patients will perform mirror therapy in two weekly sessions for 2 weeks.

An exercise program will be prescribed based on the individual's maximum heart rate, determined by polar M600^[41]^ starting just below their capacity and gradually increasing in duration and intensity. Physical activity sessions will include aerobic and stretching exercises based on the recommendations of the American Society of Sports Medicine,^[42]^ including 10 min warm-up, 40 min of effective aerobic exercise involving step, walking, and functional exercises with physiotherapy tools, and 10 min cool down including stretching exercises and a soft walk for 5 min, with deep breathing and global movements. The session will be performed twice a week for 4 weeks.

The cognitive behavioral therapy program prescribed will include group sessions of education about FM and pain perception theory, cognitive restructuring skills training, emotional stress management, and family problem resolution. All sessions will be carried out weekly for 1 h over an 8-week period.^[43]^

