In the control group, all patients will receive pharmacotherapy and a conventional treatment program based on standard education by the physician. In the first session, the patient will be evaluated on comorbidities and clinical condition, and will receive health education on pain using standard images and graphic examples. Secondly, each patient will be prescribed duloxetine 60 mg, pregabalin 300 mg, milnacipran 100 mg and vitamin D 200 mg. Each dose will be evaluated and modified in relation to the requirements of each patient and taking into account the possible adverse effects.^[44,45]^ In the final session, each patient will be prescribed cyclobenzaprine 5 mg and adverse effects and the need for new medication will again be evaluated again. This will be performed once a week for 12 weeks. To monitor adherence to treatment, patients will be contacted by phone at the end of each week of treatment.

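### As written, adverse effects and adherence are collected on different schedules and by different means in the two arms; one common weekly call would make them comparable

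*Protocol article*

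**What the plan says.** Harms (section 2.15) are collected with one instrument whose occasion of use is the session: "Patients from both groups will have a logbook available during each session". The safety trigger in the same section is also anchored to a session: "patients who show an increase in symptoms after 48 h of the session will be immediately evaluated by an rheumatologist".

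Section 2.5 (Interventions) sets the sessions. In the intervention arm:
- therapeutic neuroscience education (TNE) is given "during twice-weekly sessions for 2 weeks, each session being an average of 60 min duration";
- for mirror therapy, "Patients will perform mirror therapy in two weekly sessions for 2 weeks";
- for exercise, "The session will be performed twice a week for 4 weeks";
- for cognitive behavioural therapy (CBT), "All sessions will be carried out weekly for 1 h over an 8-week period".

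That arm also has daily tasks: booklet reading, laterality training and imagined movements. The control-group paragraph describes a weekly schedule over 12 weeks. It mentions adverse effects when doses are adjusted and again at the final session. It closes with the only adherence check in the article: "To monitor adherence to treatment, patients will be contacted by phone at the end of each week of treatment".

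Section 2.14 (Statistical analysis) says that, if there are losses or dropouts, "a statistical analysis will be carried out by protocol and intention to treat".

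**The concern.** When the occasion for recording an adverse effect is the treatment session, the number of occasions depends on the treatment. An arm that meets more often has more chances to write something down. An arm whose clinician reviews side effects, or whose patients are telephoned weekly, is prompted in a different way. Section 2.12 states that patients and physiotherapists cannot be blinded, so neither difference is masked.

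Two uses of the data are at stake. One is any report of adverse effects by arm: counts collected on unequal schedules cannot be read side by side without qualification. The other is adherence. A per-protocol analysis is planned, and if adherence enters its definition, the article describes a check for control patients and none for intervention patients. Yet the intervention arm is the one with daily practice outside the scheduled sessions to follow up.

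**Working it through.** No stated figure needs reproducing; the article gives frequencies but no session totals. The check is a count, followed by a comparison of the text for each arm.

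**Scheduled sessions (sessions per week x weeks, section 2.5)**

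| Component | Calculation | Sessions |
|---|---|---|
| TNE | 2 x 2 | 4 |
| Mirror therapy | 2 x 2 | 4 |
| Exercise | 2 x 4 | 8 |
| CBT | 1 x 8 | 8 |
| **Intervention total** | 4 + 4 + 8 + 8 | **24** |
| **Control total** | 1 x 12 | **12** |

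The ratio is 24 / 12 = 2.0. Laterality training and imagined movements are left out because the article does not say for how many weeks they run.

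**How firm is the ratio?** The article does not say which components share a day, so the range under stated assumptions is:
- All 8 CBT sessions fall on days of other components: 24 - 8 = 16 visit days, ratio 16 / 12 = 1.33.
- Greatest possible overlap: 4 exercise weeks x 2 days = 8 days carry TNE, mirror therapy and 4 of the CBT sessions. The other 4 CBT weeks add 4 days. The total is 8 + 4 = 12 visit days, ratio 1.0.
- Laterality and imagery each also have 2 sessions a week for 2 weeks (an assumption): 24 + 4 + 4 = 32 sessions, ratio 32 / 12 = 2.67.

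Counted as sessions, which is the unit in section 2.15, the intervention arm has at least 24 against 12. Counted as visit days, the excess may be smaller or absent.

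**Other means of ascertainment, as written**

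| | Intervention | Control |
|---|---|---|
| Session logbook | yes, about 24 sessions | yes, 12 sessions |
| Clinician review of adverse effects | none stated | at dose adjustment and at the final session |
| Weekly adherence call | none stated | 12 per patient |

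If the calls are for the control arm only, control patients have 12 visits + 12 calls = 24 contacts, the same number as the intervention arm's 24 sessions. The calls are meant for adherence but could bring harms to light. The imbalance in session logging and the imbalance in other prompts therefore pull in opposite directions.

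**What is unaffected.** Section 2.6 measures outcomes before treatment and at week 12 in both arms, and section 2.12 provides a blinded evaluator. Neither the sample size nor the ANCOVA draws on the logbook or the calls.

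**The case against.** The strongest reply has four parts.

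- **The instrument is the same.** Both arms get the logbook, and unequal contact is inherent when a session-based programme is compared with drug treatment. This is true, but it is a reason to add one enquiry on a common calendar. It does not make the present schedules equal.
- **No between-arm test of harms is planned.** Section 2.14 covers the primary and secondary outcomes only. This stands. The point therefore concerns whatever reporting of adverse effects by arm follows, not a stated test.
- **The call may be meant for everyone.** The sentence says only patients, and it closes a section that covers both arms. This also stands as a possibility. Its place at the end of the control paragraph makes control-only the natural reading, and a clarifying sentence would settle it.
- **Adherence in the intervention arm may be visible by other means.** Attendance can be observed, and the laterality application records accuracy and response time. The article names neither as an adherence check, and neither covers booklet reading or imagined movements.

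A reader might infer two stronger things. The first is that the intervention arm will show a spurious excess of adverse effects of some calculable size. That would need a probability of capture per session and an even two sessions a week. The article gives neither, and the control arm's reviews and calls could offset or reverse the effect. The second is that the two per-protocol groups will be selected by different rules. The article does not define the per-protocol set or link it to the calls, and leaving that definition to a fuller document is normal.

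**Conclusion.** The point holds in a limited form. On the text as it stands, harms and adherence are ascertained on different schedules (about 24 sessions against 12) and by different means (reviews and calls written for the control arm only). The count assumes that each component is logged as its own session and that the control arm's weekly schedule means 12 visits. The contrast in calls assumes that the sentence applies to the paragraph in which it stands.

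Neither the direction nor the size of any bias in harms can be determined from the document. The effect on the per-protocol analysis depends on a definition that is not shown. The primary and secondary outcome comparisons are untouched. This is a worthwhile low-cost improvement, not an error that threatens the trial's main conclusion.

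**What to change.** State in section 2.5 or 2.15 that the weekly call is made to patients in both arms for all 12 weeks, with the same fixed questions on:
- adherence, including daily practice in the intervention arm;
- adverse effects in the past week.

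Use these common weekly data for any reporting of harms by arm and for any adherence criterion in the per-protocol analysis. Keep the session logbook for immediate safety management. The calls should not be made by the blinded evaluator, because the answers would reveal the allocation.

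Cost: at most 28 patients x 12 weeks = 336 additional short calls by existing staff. If calls to both arms were already intended, the cost is one clarifying sentence and one added question on adverse effects. Treatment, outcome timing and the primary analysis do not change.
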